### Inclusion and exclusion criteria

2.2

The inclusion criteria are as follows: age, 40 to 75 years; patients with a Kellgren and Lawrence grading scale of 1 or 2 in both knee joints, (assessed on AP and lateral x-rays); those who have taken arthritis medications and have not changed their medications within the last month; applicants who have provided written consent to be a subject of this study because of the effects of KOA on their normal physical activity.

The exclusion criteria are as follows: Those who are currently being treated for clinically significant acute or chronic disorders of any of the following systems: cardiovascular, cerebrovascular, immune, respiratory, hepatobiliary, kidney and urinary, and neurological. Musculoskeletal disorders, mental, infectious or blood and neoplastic diseases. After consideration of the subject's condition, the research director may decide to allow participation in the study. A person whose arthritis is considered to be other than degenerative, as judged by the research director; a history of lower extremity fracture within the last 3 months; creatinine blood levels of more than twice the normal upper limit; patients who have received an intraarticular injection with hyaluronic acid or steroids within 3 months of the study; those whose blood levels of AST GOT or ALT GPT are more than 3 times the normal upper limit; individuals who have uncontrolled hypertension (160/100 mm Hg or more, measurement after 10 minutes at rest); individuals taking medication for a psychiatric disorder, (not including, intermittent medication for sleep disorders); individuals with a history of using herbal medicine or treatment in the last 2 weeks; patients who have received other research drugs within the last 4 weeks; patients who must continue to take drugs that are deemed to affect the results of human clinical trials; persons with a history of gastrointestinal resection (except appendectomy); those who have had artificial joint surgery; pregnant or nursing women; alcoholics or people who drink more than 4 times/week; persons with hypersensitivity to the test food or its components; any person deemed inappropriate by the research director.

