### Sample size calculation

2.4

The optimal sample size for the preliminary study and parallel design is 8 people per group. To ensure the feasibility of determining mean and variance with appropriate precision, the total sample size was maintained at 24 and divided into 3 groups.^[7]^ The pilot study will be conducted after the recruitment of 24 subjects (8 per group) who meet the selection criteria.

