### Randomization and blinding procedures

2.5

To conduct this clinical study scientifically and objectively, the final selected subjects are assigned in a ratio of 1:1:1 to experimental groups 1, 2 and a control group using block randomization. The size and number of blocks for randomization are set by the statistician and remain unknown to the researchers. The total random code is generated at about 120% of the target population. The randomized code of 3 digits (eg, PLA-R-001, PLA-R-002, PLA-R-024) is assigned in order of recruitment according to the randomization details. The test compound or placebo, packaged according to the code, is given to the subject. The randomized code cannot be used again even if the target of the randomized code is dropped. Randomization details are generated by statisticians using nQuery Advisor 7.0 (or SAS 9.0 or SPSS 21.0) and sent to the drug manufacturer. The statistician seals the randomized data for each subject in a secure envelope and sends it to the research institution.

To maintain the double-blinding, the placebo and active ingredient are identical and cannot be distinguished by appearance by the participants or staff. The code assigned to subjects will be kept sealed and will not be released until the end of the clinical trial. Cases in which the blinding must be unsealed, such as a serious adverse drug reaction, will be managed using a separate envelope created for each subject so that only their randomization is revealed. Randomization and blinding will not be revealed to the researchers until the end of the study.

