### Statistical analysis

2.9

Statistical analysis will be performed on the principle of full analysis set. For the Intention to Treat analysis, missing values will be analyzed by last observation carried forward. The baseline values before treatment and the changes in K-WOMAC at 4 and 8 weeks after treatment will be measured for each of the 2 experimental groups and the control group. To test the difference between two groups of continuous variables, an independent *t* test will be performed if the data follow a normal distribution. If not, Mann-Whitney *U* test will be performed. Paired *t* tests will be performed if the data follow a normal distribution to test the differences between groups. If not, Wilcoxon's signed-rank test will be performed. The test of normality for continuous variables will be analyzed using the Shapiro-Wilk's test. The confidence level will be set at 5%. All statistical analyses will be performed using SPSS Statistics for Windows Version 20.0 (IBM Corp., Armonk, NY).

Drinking, which can affect the weekly evaluation, is considered a management variable, and if there is a difference between groups, analysis of covariance will be performed. Descriptive statistics such as number of subjects, mean, standard deviation, minimum, median, maximum will be presented for baseline, each visit, and final evaluation, as will changes from baseline to final evaluation for continuous data, clinical laboratory tests, and vital signs. For categorical data, a division table will be provided. If necessary, 95% confidence intervals will be calculated. No intermediate analysis will be performed.

Demographic variables measured at the screening visit will be summarized for each treatment group. Assays for comparison of drug administration groups will be performed. The continuous data will be tested using the *t* tests or Wilcoxon's rank sum test. Categorical data will be analyzed using a chi-square test or Fisher exact test.

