The safety assessment calculates the rate of adverse events. Continuous data such as comparisons between groups, individual laboratory test results, and biomarkers will be analyzed using paired *t* tests or t-tests with 95% confidence intervals within the group to see if there are any changes compared to the baseline. If the distribution is not normal, nonparametric statistics (Wilcoxon signed rank test or Wilcoxon rank sum test) will be performed. Categorical data are presented as frequencies and ratios for each parameter. The difference between groups will be analyzed using the chi-square test and Fisher exact test.

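### In arms of 8, the tests named for laboratory safety data cannot reliably flag a severe rise in one to three subjects

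*Protocol article*

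**What the plan says.** The safety paragraph of section 2.9 (Statistical analysis) begins with the rate of adverse events and then turns to continuous data: "Continuous data such as comparisons between groups, individual laboratory test results, and biomarkers will be analyzed using paired" t tests or t tests. The stated purpose is detection of change: the data "will be analyzed using paired *t* tests or t-tests with 95% confidence intervals within the group to see if there are any changes compared to" baseline. If the distribution is not normal, the signed-rank or rank-sum test replaces the t test. Normality is checked by Shapiro-Wilk. On the significance level, the section says "The confidence level will be set at 5" per cent, which can only mean alpha = 0.05; it does not say one- or two-sided.

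Arm size is fixed in 2.4: "The optimal sample size for the preliminary study and parallel design is 8 people per group", and "the total sample size was maintained at 24 and divided into 3 groups".

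Three other provisions bear on the point:

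- 2.9 also gives minimum, median and maximum by visit, and names clinical laboratory tests in the same sentence.
- 2.9 and 2.11 report how many subjects had an adverse event. No laboratory value is tied to that count.
- 2.2 excludes at entry "those whose blood levels of AST GOT or ALT GPT are more than 3 times the normal upper limit", and also "creatinine blood levels of more than twice the normal upper limit". These multiples appear nowhere else.

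**The concern.** Harm to the liver or kidney from an extract need not shift a whole arm. It may appear as a large rise in one or two people. A test of mean change handles that pattern badly, because one extreme value raises the standard deviation about as fast as the mean. Rank tests discard the size of the rise altogether. With 8 per arm, a method meant to show whether laboratory values changed may return a non-significant result while one, two or even three subjects in an arm have a marked rise. The abstract presents the trial as a first step in assessing efficacy and safety, so a reader could take that result as reassurance that the data do not give.

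**Working it through.** **Inputs.** n = 8 per arm (2.4; 3 × 8 = 24 reproduces the stated total, which is not power-based). Alpha = 0.05 (2.9), taken as two-sided. Paired or two-sample t, or Wilcoxon after Shapiro-Wilk (2.9). The article gives no SD for laboratory change, so steps 1 and 2 are set up not to need one.

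**Step 1: t tests, limiting case.** Let k of 8 subjects rise by the same amount a and the others stay unchanged. The mean change is ka/8 and the variance is a²(k − k²/8)/7, so

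t = (k/8) / √[(k − k²/8)/56] = √[7k/(8 − k)].

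The size a cancels. Against a placebo arm with no change, t is the same, on 14 degrees of freedom instead of 7.

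| k affected | t | paired p (7 df) | two-sample p (14 df) |
|---|---|---|---|
| 1 | √(7/7) = 1.00 | 0.35 | 0.33 |
| 2 | √(14/6) = 1.53 | 0.17 | 0.15 |
| 3 | √(21/5) = 2.05 | 0.080 | 0.060 |
| 4 | √(28/4) = 2.65 | 0.033 | 0.019 |

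The critical values are 2.365 and 2.145, so four affected subjects are needed. One-sided paired p for k = 1, 2, 3 is 0.175, 0.085 and 0.040; a one-sided reading would rescue only k = 3. With normal noise in all subjects, the paired t test rejects for one affected subject in 4.5% of simulated data sets at a rise of 2 SD, 1.1% at 5 SD and 0.01% at 10 SD. A larger rise makes rejection less likely.

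**Step 2: the signed-rank fallback.** With one or two affected subjects and rises of 10 SD or more, Shapiro-Wilk rejects normality in 98% or more of data sets, so the rank test is the one that would usually be run. With n = 8 it reaches two-sided 5% only if the smaller rank sum is 3 or less. If the k affected subjects hold the top k ranks and the signs of the others are random, the negative ranks must sum to 3 or less. Five sets do so: none, {1}, {2}, {3} and {1, 2}. The chance is 5/2^(8−k):

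- k = 1: 5/128 = 3.9%
- k = 2: 5/64 = 7.8%
- k = 3: 5/32 = 15.6%

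With nobody affected, the test rejects in 2 × 5/256 = 3.9%. For one affected subject it therefore does no better than chance, whatever the size of the rise.

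**Step 3: simulation.** Assuming a change SD of 8 U/L and a rise of 100 U/L (12.5 SD), the signed-rank test is significant in about 4%, 8% and 15% of data sets for k = 1, 2, 3. This agrees with step 2. Mann-Whitney against placebo gives about 5%, 10% and 18%.

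**Step 4: what a count would show.** One of 8 is 12.5% (exact 95% CI 0.3% to 52.7%) and 2 of 8 is 25% (3.2% to 65.1%). Fisher's exact test against 0 of 8 gives p = 1.00 and 0.47; the first result below 0.05 is 5 of 8 (p = 0.026). The chance that an arm of 8 contains at least one case is 34% at a true rate of 5%, 57% at 10% and 90% at 25%.

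**The case against.** The strongest reply is that this concerns presentation. Tables of laboratory abnormalities commonly sit in a full protocol or statistical analysis plan, neither of which is shown, so the lack of one here is no defect. That is right, and the point does not rest on it. It rests on the method that the article does fix, which serves its stated purpose poorly for this pattern.

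A second reply is that the p values in step 1 need unaffected subjects with exactly zero change, and that real data of this shape would go to the rank test. Also right, so the rank-test rates carry the conclusion and the t values are a limit. With noise, three affected subjects are not impossible to detect by t test, hence *cannot reliably* and not *cannot*.

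A third is that a count brings no inferential gain in arms of 8. Step 4 confirms this; the gain is visibility.

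Three stronger readings are tempting but lack support:

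- *Laboratory safety is judged by t tests alone.* It is not. Maxima are displayed and subjects with adverse events are counted. A maximum would expose a single extreme value, though not how many subjects had one.
- *The plan holds its own safety limits and ignores them.* The AST/ALT and creatinine multiples in 2.2 are exclusion criteria. The article sets no on-treatment limit, so there is no contradiction.
- *The choice of dose for later work rests on this test.* No section says so. The Discussion only calls the trial a first step towards dosage and duration.

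**Conclusion.** The point holds in this limited form. The tests named in 2.9 for change in laboratory values cannot be relied on to flag a severe rise in one to three of 8 subjects. In the limiting case the paired t test gives p = 0.35, 0.17 and 0.08 regardless of size. The signed-rank test that would normally replace it detects the pattern in about 4%, 8% and 15% of data sets, so three affected subjects are missed about five times in six.

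This assumes two-sided 5% testing, full arms of 8, similar large rises in the affected subjects, and no systematic change in the rest. The signed-rank rates do not depend on the assumed SD once the rises are large relative to the noise; the quoted Mann-Whitney rates come from the simulation. The displayed maxima and adverse event counts reduce the consequence but do not give the number of subjects per arm with a marked rise. This is a worthwhile, inexpensive improvement and not a flaw that undermines the trial.

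**What to change.** In 2.9, add for each arm the number of subjects whose worst post-baseline laboratory value exceeds a pre-stated reporting cut-off, with exact 95% confidence intervals and a baseline-to-worst shift table. The multiples of the upper limit used at entry in 2.2 could serve, as reporting cut-offs only and not as rules for managing subjects. State that the mean-change and rank tests on laboratory data are descriptive, and that a non-significant result will not be read as absence of a laboratory signal.

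The cost is some wording and one extra table from data already collected, with no added visit or blood test. The downside is imprecision: counts in arms of 8 have very wide intervals and do not provide a useful significance test.

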### Study design

2.1

This study is a prospective, double-blind, single center, randomized clinical trial to determine the efficacy of PL in KOA. A total of 24 subjects with KOA will be enrolled from the Daejeon University Cheonan Korean Medicine Hospital by advertisements posted on outdoor billboards and our web site. Recruitment started in October 2019, and the trial will end in February 2020. All participants will receive a complete written explanation of the study protocol and informed consent will be obtained by the KMD of the trial.

At the screening, a medical history of the preceding 6 months will be taken and drugs consumed within the last 4 weeks will be recorded. The following blood tests will be done: glucose, complete blood count, blood urea nitrogen, creatinine, total cholesterol, aspartate transaminase (AST), alanine transaminase (ALT), alkaline phosphatase, total bilirubin, gamma (γ)-glutamyl transferase, erythrocyte sedimentation rate (ESR), high-sensitivity C-reactive protein, uric acid, rheumatoid arthritis factor, C-telopeptide of type-II collagen, triglyceride, high density lipoprotein, low density lipoprotein, electrolytes (Na, K, Cl).

Of those who meet the enrolment criteria, 24 healthy patients will be randomly assigned in a 1:1:1 ratio to treatment group 1 (PL 1,000 mg), treatment group 2 (PL 1,500 mg), and the control group (placebo). The interaction will start within 2 weeks after the screening visit.

Subjects will receive PL 1000 mg, 1500 mg or placebo for 8 weeks. The total planned duration of the trial is 8 to 10 weeks. Subjects will be assessed every 4 weeks with efficacy and safety checks at the 2nd and 3rd visits. (Table 2).

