### Outcome measures

2.7

The primary outcome will be assessed with the Korean version of the Western Ontario and McMasters Universities (K-WOMAC) osteoarthritis index which is widely used to assess knee pain, joint stiffness, and physical functioning.^[8]^ The secondary outcomes will be measured using the visual analog scale (VAS), Quality of Life Scale (EQ-5D-3L), ESR, CRP, and CTX II. VAS is a widely used tool for pain measurement. Subjects make a mark on a 100 mm straight line (0 mm = no pain, 100 mm = maximum) and the length from “no pain” to the marked point is documented. The test-re-inspection reliability is very high at 0.95.^[9]^ EQ-5D-3L is a health-related quality of life survey questionnaire. ESR is an indicator of the presence of inflammatory diseases or rheumatoid arthritis, CRP is a measure of the progression of an inflammatory disease, and C-telopeptide of type-II collagen is an indicator of bone formation. The primary and secondary outcomes will be evaluated at 4, 8, and 12 weeks after the start of the clinical trial. Safety assessments will be conducted at 4 and 8 weeks. The data of subjects is deidentified and coded by a specific program.

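### Section 2.9 mixes within-arm and between-arm tests for the biomarkers, states only a within-arm purpose, and so does not make PL versus placebo the basis for conclusions on ESR, CRP and CTX-II

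*Protocol article*

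**What the plan says.** Section 2.1 of the protocol article sets the aim: "This study is a prospective, double-blind, single center, randomized clinical trial to determine the efficacy of PL in KOA". Section 2.7 makes the three biomarkers efficacy outcomes: "The secondary outcomes will be measured using the visual analog scale (VAS), Quality of Life Scale (EQ-5D-3L), ESR, CRP, and CTX II".

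Two parts of section 2.9 bear on their analysis.

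- **General rule.** It offers an unpaired two-sample comparison for continuous variables (t test, or Mann-Whitney U where normality fails). It then brings in the paired t test, with the signed-rank test as its fallback, and gives it a between-group purpose: "tests will be performed if the data follow a normal distribution to test the differences between groups".
- **Safety paragraph.** This is the only place where a test is named for biomarkers as such. One sentence groups between-arm comparisons with laboratory values and biomarkers and offers either a paired or a plain t test for all of them. The only aim it states is to look "within the group to see if there are any changes compared to the baseline". The nonparametric fallback likewise pairs a one-sample method (signed rank) with a two-sample method (rank sum).

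**The concern.** The trial asks whether PL differs from placebo. A test of change from baseline within one arm has a different null hypothesis, namely that the mean change in that arm is zero. Placebo does not enter it. Any influence that moves all three arms alike can make that test significant in a PL arm when PL does nothing.

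The only purpose given in the biomarker sentence is the within-arm one. The same paragraph is clearer about categorical data, where it says that the difference between groups is what will be tested. For continuous data it gives no such purpose. The general rule could fill the gap, but it attaches paired tests to between-group differences and so leaves open which test answers which question.

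At stake is how three of the five secondary outcomes are read, in a trial whose Discussion hopes to inform follow-up research and possible mechanisms of action.

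**Working it through.** **Inputs**

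- Sample size: 8 per arm, 24 in total (section 2.4). The only arithmetic to reproduce is 8 × 3 = 24, which agrees. No effect size, SD or power is given there, and no figure is stated for the biomarker tests.
- Arms: PL 1,000 mg, PL 1,500 mg and placebo, 1:1:1 (section 2.1).
- Level: 5% (section 2.9, worded as a confidence level). Two-sided testing is assumed.
- Common shift d, in SDs of the change score, identical in all arms, with no PL effect. The documents give no value, so a range is shown. Changes are taken as normal.

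**Within-arm test.** For the paired t test with n = 8, the statistic is non-central t with 7 df and noncentrality d√8. The critical value is 2.365. The rejection rate is p = P(|T| > 2.365). For d = 0.5, the noncentrality is 0.5 × 2.828 = 1.41 and p = 0.232.

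**Either PL arm.** The arms are independent, so the rate is 1 − (1 − p)². For d = 0.5, 1 − 0.768² = 0.410. A simulation of 100,000 three-arm trials gave 0.411.

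**Between-arm test.** An independent t test of change, each PL arm against placebo, has 14 df. The common shift cancels in the difference, so the rate does not depend on d. The rates below are from the same simulation.

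| d | Noncentrality | Within-arm, per PL arm | Within-arm, either PL arm | Between-arm, per comparison | Between-arm, either PL arm |
|---|---|---|---|---|---|
| 0 | 0 | 5.0% | 9.7% | 5.1% | 9.1% |
| 0.25 | 0.71 | 9.4% | 18.0% | 5.1% | 9.1% |
| 0.5 | 1.41 | 23.2% | 41.1% | 4.9% | 8.9% |
| 0.8 | 2.26 | 49.6% | 74.6% | 5.0% | 9.0% |

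Like must be compared with like: 41% at d = 0.5 stands against about 9%, and 23% against about 5%. At d = 0 the two approaches barely differ. The 9.7% there comes from looking at two PL arms and is not caused by any shift.

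**Comparing significance across arms** does not repair the problem. A PL arm is significant while placebo is not in 16.3%, 31.7% and 37.2% of trials at d = 0.25, 0.5 and 0.8.

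**The case against.** A reader might infer that the plan tests biomarkers only within arms and ignores placebo. The text does not support that. The biomarker sentence itself lists comparisons between groups and names unpaired t-tests as an alternative. The rank sum test that follows is a two-sample test with no use inside one arm. The general rule in 2.9 also covers continuous variables without excluding biomarkers.

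A reader might also infer that a significant within-arm change will be reported as an effect of PL. No section says so. The plan leaves room for that reading but does not state it.

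Three further points carry weight.

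- The shift sizes are assumed. Section 2.2 sets no entry threshold on ESR, CRP or CTX-II, so the documents give no particular reason to expect regression to the mean in them. Seasonal or assay drift is conjecture.
- The sentence sits in the safety paragraph, and within-arm change is a common way to display safety laboratory values. The point is weak for those.
- Ranking the tests for secondary outcomes in a 24-person pilot is often left to the statistical analysis plan.

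The last point does not dispose of the matter. The article is not silent: it states a purpose for the biomarker test that does not answer the trial's question, and it states a wrong use for the paired test. Both are errors in the text as written.

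**Conclusion.** The point holds as a defect of specification. Section 2.9 mixes two kinds of test for the biomarkers, gives only the within-arm purpose, and blurs the general rule that might have settled the matter. It does not establish PL versus placebo as the basis for conclusions on ESR, CRP and CTX-II.

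If a within-arm test were used for that conclusion, the false-positive rate would depend on any shift common to the arms. It would be close to nominal with no shift, roughly double at 0.25 SD (9% per arm), and 23% and 50% per arm at 0.5 and 0.8 SD. These figures rest on 8 completers per arm, normal changes, two-sided 5% tests and shift sizes that the documents do not supply. They show what the wording allows, not what will happen. These are secondary outcomes of a pilot, so the point ranks as a correction that should be made and does not threaten the primary analysis.

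**What to change.** In section 2.9:

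1. State that inference on ESR, CRP and CTX-II rests on the difference in change from baseline between each PL dose and placebo, with its 95% CI, by independent t test or rank sum test.
2. Report within-arm changes of these biomarkers descriptively, and state that they are not used to claim an effect of PL.
3. Correct the paired-test sentence in the general rule, so that the paired t test and the signed-rank test are for within-group change only.

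Within-arm summaries of safety laboratory values may stay.

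The cost is the rewording of a few sentences, with no new data or patients. The downside is precision. In SDs of the change score, the 95% half-width is 2.145 × √(2/8) = 1.07 between arms and 2.365 × √(1/8) = 0.84 within an arm, so the interval is about 28% wider (1.072 / 0.836 = 1.28). Fewer biomarker results will be nominally significant.
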